**Questionnaire**										
Social-demographics	X									
Medical history	X									
Obstetric history	X									
Dietary behavior	X									X
IPAQ	X									X
Quality of life	X									X
Self-efficacy	X									X
Perceives stress	X									X
EPDS	X									X
Satisfaction										X
Food diary		X	X	X	X	X	X		X	X
**Laboratory tests**										
75 g OGTT	X									X
GA	X									X
Lipid profiles	X									X
**Glycemic measures**										
CGM measures	X	X	X	X	X	X	X			X
SMBG									X	
**Physical measures**										
Weight and BMI	X							X	X	X
Height	X									
Waist circumference	X									X
Body fat %	X									

Glycemic metrics will be calculated with values from CGM and SMBG. Participants who have signed the consent form will wear the CGM (FreeStyle Libre 1, FSL1, Abbott Diabetes Care, Inc., Alameda, CA) two times, monitoring for 7 days on week 1 and 3 days on week 6, respectively. The FSL1 is the most used biosensor for intermittent scanned CGM. All glucose data will be given each 15 min with a total of 96 readings every 24 h. From all these glucose measurements, several glucose metrics are calculated and reported on a 24-h basis average, including the percentage of time in a range from 3.9 to 10 mmol/L (TIR), percentage of time above range (TAR), percentage of time below range (TBR), a standard difference of mean glucose (SD), mean amplitude of glycemic excursions (MAGE), %CV, average glucose concentration (AG), incremental areas under the curve (iAUC), and post-prandial glycemic excursions (PE). Changes in glycemic metrics are calculated by subtracting the averaged values obtained on day 1 and 2 with CGM use at the baseline from the averaged values obtained on the second and third days of CGM use at the end-point. iAUCs will be calculated to represent the PGRs of four test meals from day 3 to 6, respectively. SMBG will be tested by glucose meter data (Qin Zhi, Sinocare, Inc., Changsha, China) six times a day in a paired test regimen at pre-meal and 1 h post-meal, at least 2 days per week from week 2 to week 5. SMBG frequency, average fasting, and pre-meal blood glucose concentrations, average 1 h post-prandial glucose concentrations (1hPG), and 1 h post-prandial excursions (1hPE) will be calculated. CGM and glucose meter data (An Wen/Qin Zhi, Sinocare, Inc. Changsha, China) will be uploaded automatically to the data platform and will be analyzed at the end of each monitoring period.

### Outcome

#### Primary outcome

The 3-h post-lunch incremental areas under the curve of post-prandial glycemic responses (iAUC) using CGM are compared between the low-GI biscuits as pre-load food (P + L) or mid-meal snack (S + L) and their isocaloric standard control of co-ingestion (CL) and placebo control (W + L) in women with recent GDM. Primary outcomes also include differences in CGM measures (AG, SD, %CV, MAGE, TIR, TAR, TBR, and PE) and GA after a 4-week intervention compared with those variables at the baseline.

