### Sample size

The sample size of the trial is estimated using PASS 15 Power Analysis and Sample Size software (NCSS, Kaysville, UT, United States). Assuming that the standard deviation (SD) is 32.9 mmol·min/L, a sample size of *n* = 39 provides 90% power to detect a change of 20 mmol·min/L in iAUC (*p* < 0.05) with Bonferroni correction, based on the previous study (36). Anticipating a 20% dropout rate, 49 subjects should be enrolled to obtain a final sample size of 39. Considering participants enrolled in four hospitals, 52 subjects will be enrolled with 13 subjects for each center.

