### Statistical analysis

The incremental areas under the curve (iAUC) will be calculated by using the trapezoidal rule (37) for PGR. All areas below pre-prandial glucose are excluded from the calculations. Two-factor repeated-measures analysis of variance (ANOVA) is performed to analyze the effects of treatment × time on outcome variables measured over the crossover study period, including iAUC for PGR and post-prandial glucose excursion. When treatment and time interaction are statistically significant, one-factor ANOVA and Bonferroni's *post-hoc* tests for multiple comparisons are performed to investigate the effect of treatment on the aforementioned measurement of PGR. Comparison between baseline and end-points is assessed by paired Student's *t*-test. Values are presented as mean ± SEM unless otherwise indicated. *P*-values of <0.05 are considered statistically significant. All analyses are performed with SPSS software version 25 (SPSS Inc., Chicago, IL, USA).

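### Nine phase 2 before–after outcomes are declared primary and each is tested at 0.05 with no hierarchy or correction, so the phase 2 false-positive rate exceeds 5%

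*Protocol article*

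**What the plan says.** The Primary outcome section opens with the phase 1 endpoint: "The 3-h post-lunch incremental areas under the curve of post-prandial glycemic responses (iAUC) using CGM are compared" between the two biscuit strategies and the two controls. It then continues: "Primary outcomes also include differences in CGM measures (AG, SD, %CV, MAGE, TIR, TAR, TBR, and PE) and GA after a 4-week intervention". The second sentence lists eight CGM measures (average glucose, standard deviation of glucose, %CV, MAGE, TIR, TAR, TBR and post-prandial excursion) plus glycated albumin, nine in all.

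The Statistical analysis section handles the before–after part in one sentence: "Comparison between baseline and end-points is assessed by paired Student's" t-test. The significance rule that follows is general: "values of <0.05 are considered statistically significant". Bonferroni appears in that section only for the phase 1 post-prandial response, where the post-hoc "tests for multiple comparisons are performed to investigate the effect of treatment on the aforementioned measurement of PGR".

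The Sample size section concerns iAUC alone. It begins "Assuming that the standard deviation (SD) is 32.9 mmol·min/L" and sets the power for iAUC "with Bonferroni correction, based on the previous study (36"). Nothing in it refers to the nine phase 2 outcomes.

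The Data collection section defines three of the nine as shares of the same monitored time: "percentage of time in a range from 3.9 to 10 mmol/L (TIR), percentage of time above range (TAR), percentage of time below range (TBR").

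**The concern.** A primary label tells the reader which results decide whether the trial met its aim. With nine such labels in phase 2 and no order among them, any one of nine P-values below 0.05 can be presented as a positive primary result. The protocol recognises multiplicity in phase 1 and corrects for it there, but gives the larger phase 2 set an unadjusted threshold.

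The choice of primary outcomes, the test and the threshold are all stated in this document. A separate analysis plan could add a correction, but the labels and the 0.05 rule as written would still stand. At stake is how much weight a significant primary result from phase 2 can bear.

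**Working it through.** **Inputs.** Nine outcomes (Primary outcome section). Paired t-test and threshold 0.05 (Statistical analysis section; two-sided is assumed, as sidedness is not stated). n = 39 evaluable, SD 32.9 and difference 20 mmol·min/L, 90% power, 20% dropout (Sample size section).

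**1. The plan's own figure, and what its Bonferroni correction covers.** Treat 32.9 as the SD of a paired difference and use n = [SD × (z for 1 − 0.05/(2k) + z for 0.90) / difference]², where k is the number of comparisons.
- k = 4, the four contrasts in the Primary outcome section: [32.9 × (2.498 + 1.282)/20]² = 38.7, so 39.
- k = 3: 37 by this formula, 40 by the exact paired t.
- k = 1, no correction: 29 by this formula, 31 by the exact paired t.
- Dropout: 39/0.8 = 48.75, so 49.

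The stated 39 is reproduced by a correction over the meal contrasts. The protocol does not state k. The correction was spent on phase 1 iAUC.

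**2. Phase 2 error rate, independent outcomes.** 1 − 0.95⁹ = 0.370. Under any dependence it cannot exceed 9 × 0.05 = 0.45. Counting only a significant change in the favourable direction: 1 − 0.975⁹ = 0.204, with upper bound 9 × 0.025 = 0.225.

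**3. Phase 2 error rate, correlated outcomes.** The nine cannot be independent. TIR, TAR and TBR sum to 100%, so any two fix the third; %CV is SD divided by mean glucose; SD and MAGE both describe variability. The protocol gives no correlations, so a range was simulated: nine equally correlated paired t-tests, n = 39, no true change, 40,000 replicates per value.

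| Assumed common correlation | At least one P < 0.05 | At least one favourable P < 0.05 |
|---|---|---|
| 0 | 37% | 20% |
| 0.3 | 33% | 17% |
| 0.5 | 27% | 14% |
| 0.7 | 20% | 10% |
| 0.9 | 13% | 6.5% |

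At zero correlation the simulation gave 37.3%, against 37.0% by formula. Equal correlation is a simplification, since the real pattern will be uneven.

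**4. Effect of correcting.** Bonferroni over nine gives 0.05/9 = 0.0056 per test. The family-wise error is then 1 − (1 − 0.0056)⁹ = 4.9% under independence and at most 5% under any dependence. At n = 39 the change detectable with 90% power rises from 0.53 to 0.68 SD of the within-woman change.

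**The case against.** The best defence is that phase 2 is not meant to be confirmatory. The Introduction describes its aim as observing before–after differences. The Figure 1 caption speaks of the 3-h iAUC as the single primary outcome, and the sample size rests on iAUC alone. The Discussion concedes that phase 2 can be neither randomized nor blinded and so cannot firmly establish which approach is better. This stands as context, but it does not remove the nine primary labels. It shows that relabelling would agree with the rest of the protocol.

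Three stronger readings are tempting, and the document does not support them.
- A reader might infer that a chance success is likely. Nine tests at 0.05 cannot exceed 45% under any dependence, 37% needs an independence that these metrics lack, and favourable results alone stay at or below 22.5%.
- A reader might infer from the diabetes exclusions that TAR is near zero and TIR near its ceiling. The protocol gives no CGM distribution for these women. The criteria admit a 2-h OGTT value between 10 and 11.1 mmol/L, and the Introduction reports raised post-prandial excursions in such women despite normal glucose tolerance.
- A reader might expect a chance finding to be reported as confirmatory. That is conjecture about later reporting.

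Sizing a trial on one outcome is ordinary practice and is not counted here as a fault. The lack of a control group in phase 2 is a separate limitation.

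**Conclusion.** The point holds in this form: nine phase 2 outcomes are primary, each is tested at 0.05, and no hierarchy or correction covers them. The false-positive rate for the set is 37% under independence and about 13–33% over assumed common correlations of 0.9 down to 0.3. Restricted to favourable changes, the figures are about 20% and 6.5–17%. These rest on two-sided tests, no true change in any of the nine, and correlations that are assumed. Even the lowest two-sided figure is about 2.5 times the nominal 5%. The inflation is real, but a false-positive primary result remains less likely than not.

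**What to change.** **Preferred.** Keep the 3-h iAUC as the sole primary outcome, in line with the Figure 1 caption and the Sample size section. Pre-specify one key phase 2 outcome and list the other eight as secondary. Post-prandial excursion or MAGE would match the stated interest in glycemic excursions, but the choice is the sponsor's. One named outcome tested at 0.05 needs no correction.

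**Alternative.** If all nine stay primary, state that Holm is applied across them.

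**Cost.** No new data or participants are needed. The trial is registered and ethics-approved, so the first option needs a documented amendment and leaves fewer outcomes with a primary claim. The second costs sensitivity: under plain Bonferroni at n = 39 the detectable change rises from about 0.53 to 0.68 SD. Holm is never less powerful than that. Neither option repairs the absence of a control group in phase 2, so a significant before–after change would still not be attributable to the tailored diet on that ground alone.

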#### Secondary outcomes

Secondary outcomes are differences in weight, glucose tolerance, dietary behaviors, quality of life, self-efficacy, perceived stress, and depression after a 4-week intervention compared with those variables at the baseline, and those differences will also be compared between two dietary strategies.

### Sample size

The sample size of the trial is estimated using PASS 15 Power Analysis and Sample Size software (NCSS, Kaysville, UT, United States). Assuming that the standard deviation (SD) is 32.9 mmol·min/L, a sample size of *n* = 39 provides 90% power to detect a change of 20 mmol·min/L in iAUC (*p* < 0.05) with Bonferroni correction, based on the previous study (36). Anticipating a 20% dropout rate, 49 subjects should be enrolled to obtain a final sample size of 39. Considering participants enrolled in four hospitals, 52 subjects will be enrolled with 13 subjects for each center.

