A dietary strategy confirmed to be effective for reducing PGR individually is of paramount importance in increasing compliance with a recommended meal plan. Therefore, to optimize the use of low-GI biscuits in reducing individual PGR and provide valuable information in clinical practice of preventing T2DM for post-partum women with recent GDM, this proposed study will be conducted in two phases. The first phase (week 1) is designed with a randomized crossover trial with the main objective to compare the effect of low-GI biscuits consumed as pre-loads or as mid-meal snacks on individual PGR of the following main meal assessed by CGM. In the second phase (weeks 2–5), individualized intervention either with pre-loads or mid-meal snacks will be conducted depending on the results of personal PGR from the first phase. The objectives of the second phase are to observe before–after differences among all participants in their glycemic control using CGM metrics and glycated albumin (GA), dietary behavior, and psychosocial factors and compare those differences between the two dietary strategies. This article presents the development of the study design and procedure.

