After removing CGM, each participant will receive a 20-min face-to-face counseling from a trained healthcare provider in each research site, including the explanation of baseline CGM glucose patterns and a comparison of PGRs of four test meals in a visual and individualized manner. Dietary advice about healthy food choices will be given as is the routine recommendation in China Medical Nutrition Therapy Guideline for Diabetes (36): (1) an appropriate amount of fish, eggs, low-fat milk, lean meat, and reduction in fatty meat in the diet, (2) more fiber-rich food, such as whole grains, vegetables, and fruits, (3) avoidance of simple sugars and refined carbohydrates, and (4) appropriate energy intake. Each participant's current status of body weight, physical activity, and dietary behaviors collected at the baseline survey will be considered in providing dietary advice.

A dietary approach of pre-load (P + L) or mid-meal snack (S + L) with lower iAUC from test results will be recommended to follow during the next 4 weeks. Considering rush time in the morning before breakfast, pre-load or snacks will be suggested to consume before lunch and dinner. For participants who are suggested to follow S + L, three Fitmeal at each morning tea and afternoon tea are asked to consume, approximately at 10 a.m. and 4 p.m., 2 h before lunch and dinner. If suggested to follow P + L, participants are asked to consume three Fitmeal 30 min before lunch and dinner, ~11:30 a.m. and 5:30 p.m. Blood glucose meter and testing supplies will be provided to participants for self-monitoring of blood glucose (SMBG) with six times a day in a manner of paired pre-meal and 1 h-post-meal, at least 2 days per week.

From week 6, participants will be invited to the research site to complete an end-point questionnaire and physical examination, another CGM will be applied to monitor glucose profile for at least 72 h, and a food diary and the time to start each meal are required to record using the log book for 2 continuous days (midnight to midnight) from the second day of applying CGM. At the end of this trial, the comprehensive glucose profiles and the impact of diet on glucose levels will be reviewed and discussed with each participant in face-to-face counseling for facilitating their understanding and compliance with the dietary strategy to stabilize glucose levels. The study flow chart can be seen in Figure 2.

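### The main objective, P+L versus S+L, is missing from the primary-outcome contrasts, and n = 39 for 90% power does not cover a Bonferroni family that includes it

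*Protocol article*

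**What the plan says.** All references are to the Protocol article.

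- **Introduction.** Phase 1 has the "main objective to compare the effect of low-GI biscuits consumed as pre-loads or as mid-meal snacks on individual PGR". The Abstract asks which of the two uses works better, and the Introduction adds that the authors know of no within-subject comparison of them.
- **Counselling and follow-up (weeks 2 to 5).** Each woman is assigned whichever of P+L and S+L gave her the lower iAUC.
- **Primary outcome.** The 3-hour post-lunch iAUC is compared between the pre-load or "mid-meal snack (S + L) and their isocaloric standard control of co-ingestion (CL) and placebo control (W + L". That gives four contrasts: P+L vs CL, P+L vs W+L, S+L vs CL and S+L vs W+L.
- **Statistical analysis.** Bonferroni post-hoc "tests for multiple comparisons are performed to investigate the effect of treatment on the aforementioned measurement of PGR". The number of pairs is not given. P-values "of <0.05 are considered statistically significant".
- **Sample size.** "Assuming that the standard deviation (SD) is 32.9 mmol·min/L", a sample of 39 "provides 90% power to detect a change of 20 mmol·min/L in iAUC", "with Bonferroni correction, based on the previous study (36"). Allowing for 20% dropout gives 49, raised to 52 across four hospitals.
- **Reference 36.** The Sample size section uses it for the previous study behind the calculation. The counselling section uses it for dietary advice given "as is the routine recommendation in China Medical Nutrition Therapy Guideline for Diabetes (36").

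**The concern.** Three sections describe three different sets of comparisons. The objective is one head-to-head contrast, the primary outcome is four contrasts against controls, and the post-hoc tests over four meals are by usual practice six pairs. The sample size applies a Bonferroni correction without saying which of these it corrects for.

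Two things are at stake. First, the contrast that answers the trial's own question is not in the primary comparison, so a claim that one strategy beats the other would rest on a test that the primary outcome does not name. Second, the stated power belongs to a particular number of comparisons. If that number leaves out the head-to-head, the 90% does not describe the analysis that answers the main objective.

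**Working it through.** **Inputs.** Difference 20 and SD 32.9 mmol·min/L, 39 completers, 20% dropout and 52 enrolled (Sample size); overall alpha 0.05 (Statistical analysis). Assumed because not stated: two-sided testing, and 32.9 as the SD of the within-woman difference. Standardised difference: d = 20/32.9 = 0.608.

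**Step 1: reproduce the 39.** With m comparisons, the normal approximation is n = [(z(1 − 0.05/(2m)) + z(0.90))/d]².

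- m = 3: [(2.394 + 1.282)/0.608]² = 36.6, so 37
- m = 4: [(2.498 + 1.282)/0.608]² = 38.65, so **39**
- m = 5: [(2.576 + 1.282)/0.608]² = 40.3, so 41
- m = 6: [(2.638 + 1.282)/0.608]² = 41.6, so 42

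The stated figure therefore reproduces for four comparisons, which is the number in the primary outcome. An exact paired t-test gives 89.6% at 39 for three comparisons, which is close. Dropout also checks: 39/0.8 = 48.75, so 49.

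**Step 2: power with t-based tests.** Noncentral t, noncentrality d√n (0.608 × √39 = 3.80), two-sided alpha 0.05/m. Degrees of freedom are n − 1 for a paired t, or 3(n − 1) if the repeated-measures error is pooled over four meals. Completers from 52 enrolled: 52 × 0.8 = 41.6, taken as 41.

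| Comparisons | Power at 39, paired t / pooled | Power at 41, paired t / pooled | n for 90%, paired t / pooled |
|---|---|---|---|
| 4 (primary outcome as listed) | 87.3% / 89.4% | 89.3% / 91.1% | 42 / 40 |
| 5 (those four plus P+L vs S+L) | 85.4% / 87.8% | 87.6% / 89.7% | 44 / 42 |
| 6 (all pairs) | 83.7% / 86.4% | 86.1% / 88.5% | 46 / 43 |

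**Step 3: the other reading of the SD.** If 32.9 is the SD of one meal's iAUC, the SD of a difference is 32.9 × √(2(1 − ρ)), where ρ is the within-woman correlation. The document gives no ρ, so these values are illustrative. For six comparisons at 39 (paired t), power is 66% at ρ = 0.3, 84% at 0.5 and 98% at 0.7; it reaches 90% at about ρ = 0.574. At ρ = 0.5 the two readings coincide, since √(2 × 0.5) = 1.

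**Step 4: reference 36.** Data collection cites references 32 to 35, Sample size cites 36 and Statistical analysis cites 37. The number is in sequence in the Sample size section. In the counselling section it appears before 32 to 35 and so is out of order.

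**The case against.** The strongest reply is that the sample size is right for the contrasts that the primary outcome lists. Four comparisons by the normal formula give 39. With pooled error, power is 89.4% at 39 and 91.1% at the 41 completers expected from 52. This stands. A reader might infer that the 90% claim is simply false, and the document does not support that: the shortfall depends on the family and on the reading of the SD.

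A second reply is that six pairs is an assumption, because the Statistical analysis section gives no count, and that under six pairs the head-to-head would be tested and corrected. This also stands. It would be too strong to say that P+L versus S+L goes untested, since the Abstract has the response compared among all four meals. But the reply leaves the conflict in place: if the head-to-head is in the family, the family has at least five members, and 39 is too few for five or six even by the normal formula (41 and 42).

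A third reply is that the shortfall is small and the extra enrolment nearly absorbs it. For five contrasts, 41 completers meet the normal-formula requirement, and the pooled-error figure is 89.7%. This is a good reason not to ask for more women. It does not supply the missing contrast.

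Finally, a reader might infer from the double use of reference 36 that the SD has no traceable source. The numbering sequence suggests that the counselling citation is the misplaced one. The reference list is not shown, so only the conflict is established.

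**Conclusion.** The contrast point holds on the text alone: the head-to-head that defines the main objective and drives phase 2 is absent from the primary-outcome contrasts, and the objective, primary outcome and post-hoc plan do not name the same comparisons.

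The power point holds conditionally. The 39 is consistent with four comparisons and is not an error of arithmetic, but it does not give 90% for a family that includes the head-to-head. The gap at 39 is about 2 to 5 percentage points for five contrasts and 4 to 6 for six; at 41 it is under 1 to about 2.5, and 1.5 to 4. These figures assume two-sided tests, Bonferroni correction, 32.9 as the SD of the paired difference and, for the pooled values, a common error variance across contrasts. If 32.9 is a single-meal SD, the direction of any error is unknown without the correlation.

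**What to change.** 1. In Primary outcome, add P+L versus S+L to the iAUC comparison.
2. Name one contrast family and use it in Primary outcome, Sample size and Statistical analysis. The four listed contrasts plus the head-to-head, with Bonferroni or Holm, would serve; all six pairs would also be coherent if stated.
3. Restate power for that family. For five contrasts, if 32.9 is confirmed as the SD of the paired difference, this is about 85% to 88% at 39 completers and 88% to 90% at 41. Keep 52 enrolled.
4. Have the sponsor confirm from its PASS input whether 32.9 is the SD of the paired difference or of a single meal, and in the latter case state the correlation assumed. The protocol should not assert either without that check.
5. Reconcile the two uses of reference 36.

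The cost is wording and a slightly less favourable power figure. No extra participants are needed.
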